#### ***7.6.5 Grades 2-4 serum creatinine elevations***

- Study drug should be permanently discontinued in the event that repeat testing of serum creatinine confirms a value equal to or higher than 2.1 mg/dL. The patient should be followed at periodic intervals not less than weekly, until the serum creatinine falls to within 0.3 mg/dL of the baseline value.

(See Appendix 3 for details)

### **7.7 Social Risk Events**

No social risk events are expected from participation in this study. However, if the Investigator learns of a social risk event, he will report the event on the Social Risk Event Form.

## **8.0 STUDY VISIT SUMMARY**

The participants will make visits to study sites for one screening, one enrollment, and 12 monthly follow-up visits. A table summarizing study procedures is available in Appendix 4.

### **8.1 Screening Visit**

The study, including potential risks and benefits of participation, will be explained to prospective participants during the screening visit and before any procedures are begun. This will include a review of the study purpose and procedures. Each woman will be asked to sign (or provide other mark) a consent form for the screening procedures, and will be given a signed copy of the consent form to take home.

All volunteers will be assigned an ID number (for the purpose of tracking their lab tests), and evaluated to determine their eligibility according to the participation eligibility criteria.

The following will be done:

- An interview with the woman to make sure she understands the study schedule and is willing to comply with study requirements
- Screening consent obtained
- Screening questionnaire
- A urine pregnancy test
- Pre-test and post-test HIV counseling
- OMT sample for HIV testing and a finger prick specimen if needed for confirmation
- Blood drawn for kidney and liver functions
- The women will be asked to return in 4 weeks for the enrollment visit, when they will receive the results of the blood tests.
- All women will be instructed in proper condom use.

## **8.2 Enrollment Visit**

If the woman meets all eligibility criteria, she will receive a detailed explanation of study procedures, and counseled in the importance of returning for follow-up. If the screening test for HIV was negative, the potential participant will be re-screened with OraQuick® on the day of enrollment. She will be asked to sign an enrollment consent form, and will be given a signed copy to take home. She will then be randomized.

The following will be done at the enrollment visit:

- An interview with the woman to make sure she understands the study schedule and is willing to comply with study requirements
- Enrollment consent obtained
- Enrollment questionnaire
- A urine pregnancy test
- Pre-test and post-test HIV counseling
- OMT sample for HIV testing and finger prick specimen if needed for confirmation
- Randomization
- Drug and condom distribution

### ***Counseling***

The counselor will review study product use, and methods of HIV/STI transmission and prevention. The use of condoms with all partners, including primary sexual contacts, will be emphasized. Staff will also stress that this is a controlled trial of a product of unknown effectiveness in the prevention of HIV transmission and that condoms should be used for all sexual contacts with all partners. This information will be repeated at each follow-up counseling session.

### ***Study Product***

Each participant will receive a supply of TDF or placebo and offered condoms. Participants will receive supplies of condoms in quantities anticipated to last until the next visit. A participant can return between scheduled visits to obtain more condoms if needed. A product-dispensing log will be maintained by the clinic and field staff to track all product distribution.

### ***Pelvic examination***

The pelvic examination will only be done if the participant has symptoms or a problem that needs to be investigated. If a wet mount is positive for *T. vaginalis*, yeast or bacterial vaginosis, the woman can be enrolled while starting treatment. Any other diagnosed curable STD can be treated and the woman enrolled. STD treatment will be recorded on the appropriate DCF.

## **8.3 Follow-up Visits**

Each participant will have a follow-up visit at a study site convenient for her and at the study clinic (months 1, 3, 6, 9, and 12). Study sites distributed throughout the study cities will be chosen as follow-up sites. Each outreach worker will be assigned to a study site and will use the site as a base of operation. The outreach worker is responsible for monthly counseling, interviewing, re-supplying the participants with products, and, if necessary, home visits to ensure that each participant completes the study. Activities at the monthly visit include:

- A questionnaire will be administered to collect information on use of product and condoms
- Participants will be counseled about product and condom use
- Participants will be re-supplied with study product and offered condoms in an amount sufficient to last until the next follow-up visit
- A pregnancy test
- Participants will provide an OMT specimen for HIV testing and a finger prick specimen if needed for confirmation

Study participants will be met at the clinic by the outreach worker for visits at months 1, 3, 6, 9, and 12 so that venous blood can be taken for the safety parameters.

If at any visit, the staff person or the study participant thinks that an examination is necessary, the participant will be referred to the study clinic for an examination.

## **8.4 Interim Contacts and Unscheduled Visits**

Participants may make interim contacts and unscheduled visits at the participant's request or as deemed necessary by the Investigator at any time during the study. All interim contacts and unscheduled visits will be documented in the participants' study records and on applicable DCF.

When an interim contact or unscheduled visit occurs in response to AEs experienced by study participants, study staff will assess the reported event clinically and provide or refer the participant to appropriate medical care.

Study participants will be instructed to contact their study clinic in the event of any adverse events (AE) except for life-threatening AE, for which participants will be instructed to seek immediate emergency care. The AE will be reported on the appropriate DCF.

Interim visits are distinguished from adverse event visits in that no health related reaction, effect, or abnormality is reported. Some examples of reasons for an interim visit are:

- To get more product or condoms
- To ask questions of study staff
- To discuss problems with study compliance
- Interim examination - examination requested but no complaints or symptom

## 9.0 STATISTICAL SUMMARY

### 9.1 Study Size Justification

#### 9.1.1 Effectiveness outcome

This study is designed to have 90% power to conclude with 95% confidence that TDF reduces the rate of HIV infection by 50% (i.e., power to obtain a one-sided 95% upper confidence limit for the rate ratio that is less than 0.5) if the true rate of reduction due to TDF is at least 83%. Recruiting 1,200 participants, and following each for 12 months, should provide the required number of incident HIV infections (30), assuming that HIV incidence in the placebo group is no less than 5/100 person-years, and follow-up is at least 80% at 12 months.

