### **3.2 Study Design**

This protocol describes a multi-center, randomized, fully-masked, parallel, placebo-controlled study of TDF for pre-exposure prophylaxis of HIV in high-risk women.

One thousand two hundred women from Douala, Cameroon, Ibadan, Nigeria and Tema, Ghana will be randomized 1:1 to once daily use of TDF 300 mg or placebo. Each country will contribute 400 participants to the study. Recruitment of participants will take about 6 months and each participant will be followed for 1 year.

HIV status will be monitored monthly. Participants will be monitored for safety using periodic physical examinations, serial laboratory tests, and adverse event queries.

In order to provide sufficient information for early safety monitoring, we will conduct laboratory tests for kidney and liver function at screening and then at months 1, 3, and then every 3 months thereafter or at their final visit if they withdraw early.

To minimize their risk of contracting HIV infection, women will be counseled monthly to use male condoms every time they have intercourse. Male latex condoms will be provided to participants. Participants converting for antibodies to HIV will be counseled and referred to medical services as appropriate for each country.

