### **9.3 Interim Analysis Plan Summary**

FHI will conduct interim analyses of safety data at 6 and 12 months after enrollment begins (see section 10.3). Each interim analysis will include comparability of masked treatment groups at enrollment, compliance with intervention, discontinuation rates, and intervention-associated morbidity.

In addition to providing safety data summaries, a biostatistician not otherwise associated with the study will perform an interim study size re-assessment calculation prior to the first interim safety analysis. S/he will make recommendations to the DMC regarding the potential need to increase study size if HIV infection or follow-up rates are lower than anticipated (a reduction in the total study size on grounds of excess power will not be permitted). Any such recommendations will be based on the infection rate pooled across both treatment groups, and not on observed differences between treatment groups; hence, no type I error rate adjustment will be required when evaluating the primary hypothesis test specified in section 9.2.1.

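### Section 9.1.1 claims 90% power with 30 infections at an 83% reduction; the claim rests on an even split of infections between arms, and actual power is about 75% (67-80% depending on the bound)

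*Protocol*

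**What the plan says.** Section 9.1.1 of the protocol sets the size of the trial for the effectiveness outcome:

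- Goal: "This study is designed to have 90% power to conclude with 95% confidence that TDF reduces the rate of HIV infection by 50" per cent, explained there as "power to obtain a one-sided 95% upper confidence limit for the rate ratio that is less than 0.5".
- Design effect: "if the true rate of reduction due to TDF is at least 83" per cent.
- Events: "Recruiting 1,200 participants, and following each for 12 months", "should provide the required number of incident HIV infections (30" in total), "assuming that HIV incidence in the placebo group is no less than 5/100 person-years, and follow-up is at least 80% at 12 months".

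Section 3.2 fixes the allocation: participants "will be randomized 1:1 to once daily use of TDF 300 mg or placebo". Section 9.2.1 makes the same comparison with 0.5 the primary test, at one-sided alpha 0.05. The bound comes from a Cox model controlling for site, with a crude incidence ratio as fallback. Section 9.3 plans a re-assessment of study size on the pooled infection rate, with recommendations "regarding the potential need to increase study size if HIV infection or follow-up rates are lower than anticipated". The formula behind the 30 infections is not given.

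**The concern.** The null rate ratio is 0.5 and the design alternative is 0.17. Under neither do infections fall equally on the two arms: 30 infections divide 10 to 20 under the null and about 4.4 to 25.6 under the alternative. The precision of a log rate ratio is governed mainly by the smaller count, so a size calculation that supposes 15 infections per arm overstates the information in 30 infections.

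At stake is the main operating characteristic of the primary test. Section 9.1.1 tells ethics committees and the data monitoring committee that the trial would miss its goal about one time in ten at the effect it was sized for. If the variance is understated, the chance is nearer one in four.

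**Working it through.** **Inputs.** One-sided alpha 0.05 (z = 1.645), power 90% (z = 1.282), null rate ratio 0.5, true rate ratio 1 − 0.83 = 0.17 and 30 infections, all from 9.1.1; 1:1 allocation from 3.2.

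**1. Reproducing the protocol's figure.** The distance from the null is ln(0.5/0.17) = 1.079, and (1.645 + 1.282)² = 8.564. With variance 4/D for the log rate ratio,

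D = 4 × 8.564 / 1.079² = 29.4, rounded to 30.

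Put back in, 30 infections give 90.5% power. So the stated pair follows from the even-split formula. A two-sided 0.05 level gives 37 events and the Freedman formula 36; neither matches.

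**2. The split under the protocol's own assumptions.** The TDF share of infections is RR/(1 + RR): 1/3 under the null and 0.17/1.17 = 0.145 under the alternative. Of 30 infections, 4.36 are then expected on TDF and 25.64 on placebo. The standard error of the log rate ratio is √(1/4.36 + 1/25.64) = 0.518, against √(4/30) = 0.365 under the even split.

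**3. Power at exactly 30 infections.** Given the total, the TDF count is binomial. The Wald upper limit for x infections on TDF is x/(30 − x) × exp{1.645 √(1/x + 1/(30 − x))}.

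| Success if TDF infections are at most | Wald upper limit at that count | One-sided error at RR 0.5 | Power at RR 0.17 |
|---|---|---|---|
| 5 | 0.448 | 3.5% | 73.6% |
| 6 | 0.530 | 8.4% | 86.5% |
| 7 | 0.619 | 16.7% | 94.0% |

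Exact, mid-P, Wald, score and likelihood-ratio rules all set the limit at 5, so power is 73.6%. The first cut-off to exceed 90% power is 7, with an error of 16.7% and an upper limit well above 0.5.

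**4. Expected infections.** The protocol does not say how 80% follow-up converts to person-time. I take 480 to 540 person-years per arm (600 × 0.8 to 600 × 0.9):

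- 480: 24.0 on placebo + 4.1 on TDF = 28.1
- 540: 27.0 on placebo + 4.6 on TDF = 31.6

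Thirty is therefore a sound forecast of the number of infections. The fault lies in the number required.

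**5. Power with a random event total (means 28.1 to 31.6).**

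- Exact: 67-73%
- Wald: 72-77%
- Score: 73-78%
- Mid-P: 74-79%
- Likelihood ratio: 76-80%

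**6. The planned Cox analysis, simulated with a Wald bound.** Without site terms, power was 76.4% under the protocol's accrual assumptions (mean 30.8 infections, 6,000 runs) and 78.6% at exactly 30 infections. Stratified by site and with monthly midpoint dating, it was 76.7%.

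**7. What 90% would take.** At an 83% reduction with a random total, the mean number of infections needed runs from 44 (likelihood ratio) to 49 (exact). With a fixed total, exact power first reaches 90% at 44, dips below it at some larger totals because counts are discrete, and stays above it from 51. With 30 infections, the rule of 5 or fewer gives 90% power at a true reduction of 87.8%. The Cox Wald simulation also gives 90% at a rate ratio of 0.12.

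**The case against.** The strongest reply is that the figure is no slip: a standard formula yields 30 and 90%. That stands. A reader might infer an arithmetic mistake, but the documents do not show one. The weakness is the use of an even-split variance where neither the null nor the alternative gives an even split.

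A second reply is that no single power value is fixed, because section 9.2 leaves the appropriateness of test statistics to a masked review. That also stands and is why a range is given. The whole range lies below 90%.

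A third is that the inputs are floors: incidence, retention and effect could all be better than stated. Better values would raise power, but the claim of 90% is attached to 30 infections and an 83% reduction. Reading 30 as placebo infections only, about 35 in total, still gives only about 80%.

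Two stronger readings should be resisted.

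- Putting the variance at the alternative into the normal formula gives 59 infections for 90% power (and 67% power at 30). This errs in the other direction: 59 infections give about 96% power under the count-based rules.
- One might say that the section 9.3 re-assessment will aim at 30 infections. Section 9.3 names no event target; it speaks only of rates lower than anticipated. That 30 would be carried into it is a risk, not something the protocol states.

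**Conclusion.** The power statement in 9.1.1 is wrong as written. With about 30 infections and a true reduction of 83%, power is about 75%: 73.6% by the exact calculation at exactly 30, about 77% for the planned Cox Wald bound, and 67-80% over bounds and plausible event totals. The shortfall is roughly 10 to 23 percentage points, and the chance of missing the goal at the design effect is between one in five and one in three, not one in ten.

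This rests on constant hazards and on 480 to 540 person-years per arm for 80% follow-up. The 73.6% needs only the stated rate ratios, equal person-time in the two arms and 30 infections. The finding does not touch the validity of the primary test, the event forecast or the planned enrolment.

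**What to change.** - In 9.1.1, state that with about 30 expected infections power is about 75% if the true reduction is 83% (range about 67-80%, with the confidence bound named), and about 90% if it is about 88%.
- Replace the 30 required infections with the number that matches the claimed power, about 44-51 for 90% at 83% depending on the bound, or describe 30 as the expected number.
- If the section 9.3 re-assessment uses an event target, give it the corrected one. That procedure can only increase the study size, and a target of 30 could signal that the size is adequate when power is only in the 70s.

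The cost is wording in 9.1.1, and in 9.3 if a target is used, together with a less favourable stated power. Correcting the statement requires no change in enrolment, test or follow-up. Whether to accept the lower power or seek more infections is a separate decision for the sponsor.

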#### 9.1.2 Safety outcomes

We will assess safety outcomes by treatment group (pooled across sites), as well as in each site-by-treatment group cohort. Site-level information will be assessed to provide each country's public health sector with data to make informed safety decisions in their own populations. As demonstrated in Table 1, precise estimates of 12-month event probabilities should be obtained at the site-level using the chosen study size. Furthermore, the study size is adequate to observe toxicity outcomes that occur at a modest rate of 5%; the probability that five or more such events are observed among a cohort of 200 participants is greater than 95%.

Table 1: 95% Confidence intervals corresponding to 12-month safety event probability estimates, assuming 20% loss to follow-up.

| If estimated 12-month cumulative probability is equal to... | Then the 95% confidence interval is... |                |
|-------------------------------------------------------------|----------------------------------------|----------------|
|                                                             | Site-level (N=200)                     | Pooled (N=600) |
| 1%                                                          | (>.000, .024)                          | (.002, .018)   |
| 2%                                                          | (>.000, .040)                          | (.008, .032)   |
| 3%                                                          | (.005, .055)                           | (.016, .044)   |
| 5%                                                          | (.018, .082)                           | (.032, .068)   |
| 10%                                                         | (.056, .144)                           | (.075, .125)   |

## 9.2 Analysis Plan Summary

A detailed analysis plan that covers both the final analysis and the planned interim analyses will be developed and approved prior to initiation of the study. The following is a summary of the planned analyses. Any deviations to be made from this summary plan will be documented in the detailed analysis plan.

All primary and most secondary analyses will be conducted on an intent-to-treat basis. However, in order to assess the effectiveness and safety of TDF among those participants who complied with key aspects of the study protocol and to evaluate the potential impact of treatment on loss to follow-up, various additional analysis populations may be defined in the detailed analysis plan. Any key decisions regarding the timing of outcomes, the appropriateness of test statistics or model assumptions, or any other statistical issues will be made in a masked review of the data (i.e., masked to the true treatment assignments). Unmasking with respect treatment assignment will only be done for the final interpretation of the results, unless otherwise required by the data monitoring committee (DMC) (see section 10.3).

### 9.2.1 Analysis of effectiveness outcomes

All primary analyses will be conducted on an intent-to-treat basis. Incidence rates of HIV infection in the two treatment groups will be calculated, and the effect of TDF on the incidence of infection will be determined by calculating an upper 95% confidence bound for the rate ratio (TDF *versus* placebo). This upper confidence bound will be compared to 0.5 to test the hypothesis that the reduction in the HIV infection rate due to TDF is at least 50% (i.e., a one-sided test of superiority with  $\alpha = 0.05$ ). The estimated rate ratio and 95% confidence bound will be obtained using Cox proportional hazards regression, controlling for site, if the model assumptions are found to be appropriate. Otherwise, crude incidence ratio estimates and confidence bounds will be obtained based on the ratio of the numbers of new cases to the total lengths of treatment exposure. Time to HIV infection, in days, will be computed as the difference between the date of HIV infection, estimated using the midpoint of the study interval in which the first positive HIV test was obtained (see Section 6.1) and the enrollment date, plus one. Potential prognostic factors identified prior to study initiation will be adjusted for in supporting analyses of incident infections. Likewise, supporting analyses will evaluate the treatment effect across sites by introducing treatment-by-site interaction terms to the proportional hazards regression model.

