#### **Study product interruption**

Treatment with the study product may be interrupted temporarily or permanently for any of the following reasons:

- The participant ran out of supplies for whatever reason (e.g., she missed a visit); in this case the date of interruption is the date of her last product use
- An adverse event
- The Investigator decides to withdraw the study product temporarily in the interests of the safety and well being of the participant

- The participant considers it to be in her best interest not to use the study product
- Pregnancy
- The participant becomes HIV positive

Whenever the study product is interrupted, the information will be noted on the follow-up DCF. For all except the first reason listed above, the date of the interruption is the date on which the Investigator decides to interrupt the treatment and if possible, follow-up should be continued until resolution of the AE. **If possible, participants will be tested for HIV so that the status is determined at the time of product interruption.**

Participants who have had study drug interruption may resume study product use and will be given the study product to which they were originally randomized. **At the time of product resumption the participant will be tested for HIV so that status is determined.**

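### The fallback for the primary HIV analysis divides infections by time on treatment and drops site, which conflicts with the intent-to-treat statement in the same section

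*Protocol*

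**What the plan says.** Protocol section 9.2.1 states: "All primary analyses will be conducted on an intent-to-treat basis". The effect of TDF is judged by an upper 95% confidence bound for the TDF/placebo rate ratio, compared with 0.5 ("a one-sided test of superiority with" alpha 0.05). The bound comes from a Cox model controlling for site, provided its assumptions are found suitable. If they are not, crude incidence ratios and bounds are used instead, "based on the ratio of the numbers of new cases to the total lengths of treatment exposure".

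Four other places bear on this:
- **Section 3.6.1, with its part on study product interruption:** product may be stopped for a time or for good, for several reasons. It is withdrawn in pregnancy.
- **End of section 4.2:** efficacy is assessed to the last follow-up visit, not to the last dose.
- **Section 3.3.1:** randomisation is stratified by site.
- **Section 9.2:** decisions on timing of outcomes, test statistics and model assumptions "will be made in a masked review of the data (i.e., masked to the true treatment assignments").

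**The concern.** An intent-to-treat rate counts every infection over all the time in which an infection could have been observed. The fallback keeps all new cases but names a different denominator. Because product use can end before follow-up does, time on treatment and time at risk are not the same quantity. Taken as written, a woman who stops product, stays in follow-up and is then infected adds a case, but none of her time since stopping.

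The primary decision rests on one bound compared with one number, 0.5. A denominator that differs by arm for reasons unrelated to infection risk moves that bound directly, in a direction set by which arm stops product more. The fallback also gives up the adjustment for site that the main model carries.

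**Working it through.** **Inputs from the protocol.** 1,200 women randomised 1:1, followed 12 months; placebo incidence 5 per 100 person-years; at least 80% follow-up at 12 months; true reduction 83% (rate ratio 0.17); 30 infections required (sections 3.2 and 9.1.1). The criterion is "power to obtain a one-sided 95% upper confidence limit for the rate ratio that is less than 0.5".

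**The plan's own figure.** One-sided alpha 0.05, power 90%, null ratio 0.5, equal allocation:

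events = (1.645 + 1.282)² / (0.25 × [ln(0.17/0.5)]²) = 29.43, rounded up to 30.

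The stated 30 is reproduced, so this point does not touch the sample size calculation.

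**Effect of the denominator.** Let fT and fP be the shares of follow-up time spent on product in the TDF and placebo arms, and a and b the infections. Then

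fallback ratio = [a / (fT × PY_T)] / [b / (fP × PY_P)] = (ratio on time at risk) × fP/fT.

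Equal shares cancel. Unequal shares multiply both the estimate and its bound by fP/fT.

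**Size.** The protocol gives no on-product shares, so those below are assumptions. With loss assumed linear down to 80%, mean follow-up is 90% of 600, or 540 person-years per arm. Expected placebo infections are 540 × 0.05 = 27. Expected TDF infections are 13.5 at a ratio of 0.5 and 4.59 at 0.17. I enumerated two independent Poisson counts with the bound

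(a/b) × (fP/fT) × exp(1.645 × √(1/a + 1/b)),

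replacing a = 0 by 0.5. The Wald form is my assumption; the protocol does not name one.

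| TDF share | Placebo share | Multiplier | Ratio 0.5 becomes | P(bound < 0.5) at true ratio 0.5 | P(bound < 0.5) at true ratio 0.17 |
|---|---|---|---|---|---|
| equal | equal | 1.000 | 0.500 | 4.2% | 76.5% |
| 80% | 90% | 1.125 | 0.562 | 1.9% | 64.5% |
| 90% | 80% | 0.889 | 0.444 | 8.8% | 85.4% |
| 90% | 70% | 0.778 | 0.389 | 17.2% | 92.1% |

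The last column should be read as change from the first row. That row lies below the planned 90% because the 30-event formula uses an equal-split variance, which is a separate matter.

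**Single data sets.** With 5 TDF and 25 placebo infections, the bound on time at risk is 0.20 × exp(1.645 × √0.24) = 0.448. At shares of 80% and 90% it is 0.448 × 1.125 = 0.504, which crosses 0.5. With 5 and 26, the same step goes from 0.429 to 0.483 and the conclusion stands.

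**Effect of dropping site.** If person-time is equal between arms within each site, the crude ratio equals the site-specific ratio. Now assume site rates of 2, 5 and 8 per 100 person-years and opposite loss patterns (TDF 190/180/160, placebo 160/180/190 person-years; 530 per arm). Crude ratio = 0.5 × (3.8 + 9.0 + 12.8) / (3.2 + 9.0 + 15.2) = 0.5 × 25.6/27.4 = 0.467.

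**The case against.** The best defence is that the denominator phrase is loose wording for person-time in the assigned arm. The intent-to-treat sentence and the follow-up rule then govern, and nothing is wrong. That reading is possible, and it is why the point is a conflict in wording rather than a stated departure from intent-to-treat. It does not remove the need to correct the phrase, because the literal reading changes the primary decision rule.

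The size can also be challenged. The bias needs unequal on-product shares. The tolerability data in section 3.4 are mostly close to placebo (nausea 11% v 10%, diarrhea 9% v 8%, vomiting 5% v 2%), so a ten-point gap has no support in the document. The change of conclusion at 5 v 25 needs a result near the boundary. Both remarks stand; the figures are a range, not a forecast.

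A reader might infer more than the protocol supports:
- **That the fallback is an as-treated analysis.** Women stay in their randomised arm and all new cases count. The literal result is intent-to-treat cases over on-product time.
- **That the method is chosen after outcomes are seen by coded arm.** Section 9.2 says only that the review is masked to true assignments. The mentions of a final masked analysis (3.3.4) and masked treatment groups (9.3) make coded groups likely, but nothing says that reviewers see infections by coded arm. The detailed plan may hold a switching criterion. If the more favourable denominator were always picked, with the exposure ratio varying by an assumed 5-10%, type I error would be 4.9-5.8%, against 4.2%.
- **That a person-time bound is no remedy for non-proportional hazards.** It targets the ratio of average rates. In simulations of four non-proportional patterns with up to four-fold hazard changes within the year, the one-sided 95% bound missed that ratio 4.1-4.5% of the time.
- **That zero TDF infections would leave no bound.** This presumes a Wald bound, which the protocol does not name.
- **That the rule for dating interruptions distorts efficacy** ("the date of the interruption is the date on which the Investigator decides to interrupt the treatment"). Nothing ties that date to the efficacy denominator.

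**Conclusion.** The point holds as a conflict within the protocol. The fallback's denominator, as worded, does not fit the intent-to-treat statement in the same section or efficacy follow-up to the last visit. It matters only if the Cox model is set aside, the phrase is applied literally, and on-product shares differ by arm. In that case type I error at a true ratio of 0.5 runs from 1.9% to 17.2% over the three unequal pairs shown, against 4.2% with time at risk. It can be conservative or anti-conservative. These figures rest on assumed shares, 540 person-years per arm and a Wald bound.

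The loss of site adjustment is a lesser inconsistency. It has no effect with person-time balanced within sites, and moved 0.50 to 0.467 under a deliberately adverse pattern. The main Cox analysis and the 30-event target are unaffected.

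**What to change.** In section 9.2.1, define the fallback denominator as person-time from enrollment to infection or last HIV test, regardless of product use, and stratify the rate ratio by site. Preferably, keep the site-controlled Cox model as the single primary method whatever the check of its assumptions shows, with the rate ratio as support. If the switch is kept, fix its criterion before any outcome data are reviewed by arm. An analysis over time on product can still be reported if labelled as supporting.

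The cost is a change of wording in the protocol and the matching text of the detailed analysis plan. Enrollment, infection and HIV test dates are already collected, so no new data are needed.
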